**Figure 1 F1:**
[figure not shown]

### Sample

Twenty-six women, regardless of their race and/or social class, above the age of 65 who are community residents and classified as pre-frail according to the criteria established by Fried et al. (2001) will be selected for inclusion in the study. These volunteers will be randomly divided into two groups (control = C and experimental = E) of 13 volunteers each. This population was chosen based upon the assumption that pre-frail elderly people appear to respond better to interventions, resulting in a greater possibility of modifications that influence muscle response.^3 ^Demographic characteristics (age, race, school level, height, weight and body mass index) will be collected from all the participants.

Elderly women who meet one or more of the following criteria will be excluded from the study: previous lower extremities orthopedic surgery, a history of fractures within the past year, an inability to walk unaided, carriers of neurological diseases, diagnosed acute inflammatory disease that could interfere in the assessments and the program, tumor growth in the last five years, current use of immunomodulating medications and cognitive impairment based on the mini-mental state examination [31].

### Primary outcome

Plasma levels of IL-6 and TNF-α will be determined using the ELISA (*enzyme-linked immuno sorbent assay*) method with high sensitivity kits (Quantikine^®^HS, R&D Systems Minneapolis, USA). Samples will be read with an adjusted microplate reader for 490 nm and wavelength correction to 650 nm. TNF-α acts at two known receptors: TNFR1 and TNFR2. In humans, the measure of circulating levels of the two soluble receptors is useful in determining the global production of TNF-α in plasma [32].

### Secondary outcomes

For functional performance, the Timed Up and Go (TUG) test [25,30,33] and the 10-Meter Walk Test (10MWT) will be used [34]. The TUG test has a high test-retest and inter-examiner reliability (ICC = 0.99, r = 0.93) [35]. Skinkai (2000) asserted that the 10MWT is the greatest predictor of falls and functional dependency in the elderly [34].

Knee extensor muscle strength will be evaluated with the Biodex system 3 *Pro*^*® *^isokinetic dynamometer at angular speeds of 60 and 180°/s. This equipment is capable of evaluating muscle function in concentric, eccentric and isometric modes at angular speeds of 2 to 420°/s. It will be used to measure the maximum work produced by the knee extensor muscle group normalized to body weight in the concentric and at angular speeds of 60 and 180°/s. Peak torque and potential at these speeds will also be assessed. The advantages of using an isokinetic dynamometer include using the same resistance at one constant speed of motion, a high reliability in the measures and a correlation between the torque, work and potential parameters (ICC = 0.99, p < 0.01) [35].

### Randomization

After the initial evaluation, the volunteers will be randomized into either group E or group C. This randomization will take place with an equal number of envelopes. The researcher responsible for the evaluations will be blinded to the participants' group. The researcher responsible for the intervention will be blinded to the assessment results until the final data collection.

### Intervention

The volunteers in experimental group will begin the physical activity program of exercises conducted in small groups with direct instruction from the physical therapist for one hour, three times per week for a period of ten weeks. The large muscle groups of the lower extremities (hip flexors and extensors, knee flexors and extensors and plantar flexors) will be exercised on an open and closed kinetic chain. The appropriate weight for each volunteer will be determined by calculating the percent of maximum load (1RM) [25]. The choice of concentric exercises was based upon literature which has indicated that this activity in the large muscle groups induces and modifies the production of IL-6 and TNF-α [3,12,19,28]. Semi-squats are used for their increased functional benefits and because they decrease the compression forces on the patellofemoral joint, thereby minimizing the risk of pain [22]. The session will begin with ten minutes of walking as a warm-up. Next, hip flexion, extension, abduction and adduction and knee flexion and extension motions will be conducted in an open kinematic chain, along with a semi-squat, aimed at strengthening the muscles of the lower extremities [25]. Hip exercises will be conducted in the supine (hip flexion and adduction), lateral (hip abduction) and prone (hip extension and knee flexion) positions. The semi-squat exercises will be conducted while standing with up to 60 degrees of knee flexion and with bilateral support. The concentric knee extension exercises will be conducted with the volunteer seated. The feet remained on the floor, maintaining an initial knee angle of 70 degrees of flexion. They will be instructed to extend the knee from 70 to 20 degrees of flexion, without terminally extending the knee. The program will consist of a total of 30 one-hour sessions, conducted three times per week over ten weeks. At the end of each training day, relaxation and cool-down exercises will be performed.

The volunteers in control group will be instructed to refrain from beginning any type of new physical activity for a period of the study, maintaining the activities of their normal daily lives.

After ten weeks, all the volunteers will be reevaluated with the same tests and parameters conducted in the first assessment. After this reevaluation, the groups will switch and those women who had completed the exercise program (experimental group) will now remain inactive. Those women who had previously been inactive (control group) will begin the same resistance program the experimental group had performed (Figure 1).

### RM calculation

In the first session, the maximum resistance test (RM) will be conducted for each volunteer using the 1RM test for knee extension and flexion. For the knee extension test, the volunteer will be asked to sit on a standard stretcher, in the same manner that was previously described for the concentric knee extension exercise. One leg weight of 1 kg will be placed on the ankle of the dominant leg, and the volunteer will be instructed to extend the knee fully, without changing or increasing the speed of the motion, from the starting position of 90 degrees of flexion with the foot on the floor. A rest period of five minutes will be given and the motion will then be repeated with an increase of 1 or 2 kg, according to the degree of difficulty reported by the volunteer. The maximum load will be considered to be the weight at which the volunteer is unable to perform the motion to its fullest extent, shows signs of fatigue and/or increases the speed of the motion, with no more than five attempts made throughout the day. With the RM established for knee extension, the work percentage will be calculated. In the first six sessions, 50% of 1RM will be used. Beginning with the seventh session, the load used will be increased to 75% of 1RM [25]. Every two weeks, or every six sessions, a new 1RM test will be conducted to adjust the load. Three sets of eight repetitions for each one of the exercises will be standardized in relation to the workload, as described in previous studies [25].

For calculating the 1RM for the knee flexors, the volunteer will be placed in the prone position and instructed to flex the knee from 0 degrees to 45 degrees. The same parameters as previously described in relation to the load, interval and observation of the executed motion will be considered in order to establish the RM for the knee flexors. The same percentage of 50% and 75% of 1RM will be used for the work.

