Thus, this randomized crossover clinical trial was proposed with the objective of verifying the effect of a program of muscle strengthening with load during a ten week period in pre-frail elderly women with attention to the following outcomes: (1) functional ability, (2) knee extensor muscle strength and (3) plasma levels of IL-6 and TNF-α. The study hypothesis is grounded in the assumption that exercising with 75% of the maximum load at a frequency of three times per week for 10 weeks may be sufficient to provide strength gains, and consequently improve functional ability and reduce the plasma levels of IL-6 and TNF-α.

This project has financial support from the Conselho Nacional de Desenvolvimento Científico e Tecnológico - CNPq, Brasília, Brasil.

Clinical Trial Registration: ISRCTN62824599.

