## Methods/Design

The general objective of the study will be verified the effect of a program of resistance exercises at 75% RM on the functional capacity, knee extensor muscle strength, and to measure the plasma levels of IL-6 and sTNFr in pre-frail elderly women.

Questions/Hypotheses

1. Among pre-frail elderly women, will changes occur in the plasma levels of the inflammatory mediators IL-6 and sTNFr, functional capacity and knee extensor muscle strength after completing a program of resistance exercises at 75% of 1RM, three times a week, for 10 weeks?

2. In a follow-up three months after finishing the training, will there be modifications in the functional capacity, knee extensor muscle strength and the plasma levels of IL-6 and sTNFr in pre-frail elderly women?

3. Is there a correlation between functional capacity, knee extensor muscle strength and plasma levels of IL-6 and sTNFr before and after a training program with load in pre-frail elderly women?

The study design is a blind randomized crossover clinical trial. Participants will be recruited from two universities. An initial assessment will be undertaken after recruitment and prior to randomization into either experimental or control group. Participants in the experimental group will receive an exercise program, three times a week, during ten weeks. Participants in the control group will receive no physiotherapy intervention. Outcomes will be measured again after ten weeks to reflect the immediate effect of the intervention. Then, the experimental group will receive no physiotherapy intervention and the control group will receive the same exercise program. Outcomes will be measured again to reflect longer-term outcomes from experimental group and the immediate effect of the intervention in the control group (Figure 1). This allows verification of the existence of a change and/or variable correlations specifically due to the intervention, and not due to the time factor and/or changes in the aging process. Furthermore, it allows verification of the existence of variable changes after finishing the training. Additionally, from an ethical point of view, it guarantees that the volunteers receive the same treatment. The outcome measures will be collected by a physiotherapist who was blind to group allocation. The responsible for the intervention will not know about the assessment. The study was approved by the ethical committee of the university and informed consent procedures were taken.

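### Minor: when a 1RM test ends in an incomplete lift, the failed weight is recorded as the maximum, so the nominal 50% and 75% loads exceed those percentages of the true maximum by up to 0.5 or 0.75 of one weight step

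*Protocol article*

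**What the plan says.** The protocol article states the dose as a percentage of maximum load. The hypothesis in the Background speaks of "exercising with 75% of the maximum load at a frequency of three times per week for 10 weeks", and the first study question in Methods/Design asks about changes "after completing a program of resistance exercises at 75% of 1RM". The Intervention section sets each woman's weight from a percentage of maximum load and treats maximum load and 1RM as the same thing. (The Abstract gives a different range, 50 to 70% of 1RM. That is a separate matter and is not used here.)

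The RM calculation section describes the test. It begins lightly: "One leg weight of 1 kg will be placed on the ankle of the dominant leg". After a five-minute rest the motion is repeated "with an increase of 1 or 2 kg, according to the degree of difficulty reported by the volunteer". The section then fixes the result: "The maximum load will be considered to be the weight at which the volunteer is unable to perform the motion to its fullest extent". Two further endings follow in the same sentence, namely that she "shows signs of fatigue and/or increases the speed of the motion", and attempts are capped at five in a day. Training uses 50% of the recorded value in sessions 1 to 6 and 75% from session 7. The test is repeated every six sessions, with no different recording rule given. The knee flexor 1RM, tested from 0 to 45 degrees, follows the same parameters and percentages.

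**The concern.** A one-repetition maximum is ordinarily the heaviest weight a person can lift once. The first ending in the RM calculation section records instead a weight that she could not lift through the range. No sentence goes back to the last weight she completed. In those tests the reference is too high, so the stated percentage is too low a description of the load she trains with.

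Intensity matters in this trial. The hypothesis names it, and the Background and Conclusions say that the right intensity is not yet established. The Conclusions also say the trial was designed to be reproducible in research and in the clinic. Someone who takes 75% of 1RM in its ordinary sense would prescribe a lighter load than the affected women received. The participants are pre-frail women over 65, so it also matters whether a load rests on a weight each has actually lifted.

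**Working it through.** **Inputs, all from the RM calculation section unless noted.** Start at 1 kg; step s = 1 or 2 kg; at most five attempts; load fraction p = 0.50 (sessions 1 to 6) or 0.75 (from session 7). With 30 sessions in all (Intervention section), 30 − 6 = 24 sessions are at nominal 75%. The protocol gives no typical 1RM, so the values of L below are illustrations.

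**Set-up.** Let L be the last weight completed and L + s the weight at which the lift is incomplete. Had the earlier weight met a stopping sign, the test would have ended there, so L was completed to the standard. The true maximum M for the tested motion therefore satisfies L ≤ M < L + s, and the value recorded is L + s. This assumes that the failure reflects her maximum and not tiredness from earlier attempts; the five-minute rest makes that reasonable.

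**Excess load in kg.** Excess = p(L + s) − pM = p(L + s − M). It is above 0 and at most ps:
- p = 0.75: at most 0.75 × 1 = 0.75 kg, or 0.75 × 2 = 1.5 kg
- p = 0.50: at most 0.50 × 1 = 0.5 kg, or 0.50 × 2 = 1.0 kg

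Enumerating every ladder from 1 kg with steps of 1 or 2 kg and at most five attempts gives exactly these maxima. It never gives an excess of zero or below.

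**Excess as a percentage.** The true percentage behind a nominal 75% is 75(L + s)/M. It is 75(L + s)/(L + s/2) if M lies midway (an assumption), and 75(L + s)/L at most.

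| L (kg) | s (kg) | Load 0.75(L + s) (kg) | M midway | Upper bound (M = L) |
|---|---|---|---|---|
| 5 | 1 | 4.5 | 81.8% | 90.0% |
| 7 | 1 | 6.0 | 80.0% | 85.7% |
| 9 | 1 | 7.5 | 78.9% | 83.3% |
| 5 | 2 | 5.25 | 87.5% | 105.0% |
| 7 | 2 | 6.75 | 84.4% | 96.4% |

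The largest L that can precede a failure is 1 + 3 × 2 = 7 kg if the opening lift counts among the five attempts. It is 1 + 4 × 2 = 9 kg if it does not; the protocol does not say. Re-tests may start above 1 kg, and L can then be larger and the excess smaller: L = 12, s = 1 gives 78.0% midway. At nominal 50% with s = 1, the midway values are 54.5% (L = 5), 53.3% (L = 7) and 52.6% (L = 9).

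**When the load exceeds anything she has lifted.** 0.75(L + s) > L when L < 3s, that is, L below 3 kg with a 1 kg step or below 6 kg with a 2 kg step. At nominal 50% this needs L < s.

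**The alternative rule.** If L is recorded, the percentage at the midpoint is 75L/(L + s/2). With s = 1 this is 68.2% (L = 5), 70.0% (L = 7) and 71.1% (L = 9). The error is 75(s/2)/(L + s/2) = 6.8, 5.0 and 3.9 points, positive under the present rule and negative under the alternative.

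**The case against.** The strongest case on the other side is that this changes nothing the trial measures. Knee strength is taken on the isokinetic dynamometer, and 1RM enters no endpoint, the sample size or the analysis. That stands, and it is why the point is minor.

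A reader might infer that the trial as a whole trains above 75%. The document does not support this. A test ended by fatigue or speed on a completed lift does not record a failed weight. A woman who completes every attempt stops at 5 to 9 kg (6 to 11 kg if the opening lift is not counted), which may be below her maximum. The share of tests ending each way is unknown, and so is the net direction.

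A reader might also take 79 to 80% as a floor on the true intensity. It is one only for affected tests, with M midway and re-tests starting at 1 kg. As M approaches the failed weight, the excess approaches zero.

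For knee extension the point is blunted. The test runs from 90 degrees to full extension, but in training she is to "extend the knee from 70 to 20 degrees of flexion, without terminally extending the knee". A woman who fails only the last degrees may manage that weight through the trained arc. No shorter arc is stated for flexion.

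The safety argument is thin except at low weights. In each 1 kg-step row above, the load is below L. Training is directly supervised and begins at 50%.

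Finally, it can be said that the rule is defined and can be followed as written, and that the source cited for the percentage method may use the same rule. That source is not at hand, so no departure from it is claimed. The section still calls the result 1RM, and the hypothesis and study question quote the percentage without saying that its base is a failed lift.

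**Conclusion.** The rule is wrong as written, but the consequence is minor. In a test that ends in an incomplete lift, the nominal loads exceed 50% and 75% of the true maximum for the tested motion by more than zero and at most 0.5s or 0.75s kg, with s of 1 or 2 kg. These bounds follow from the text and need only the assumption that the failed lift reflects the woman's maximum. The percentage figures also depend on assumed values of L and on where M lies within the step.

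The conclusion is firm for knee flexion. For knee extension it holds for the tested motion but not necessarily for the trained arc. It would be a mistake to read this as a bias in the comparison of exercise with no exercise: the matter is how the dose is labelled and, when L < 3s, a load heavier than any weight the woman has lifted.

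**What to change.** In the RM calculation section, define 1RM as the heaviest weight lifted through the full range to the standard, for extensors and flexors and at every re-test. Record both the last completed and the failed weight, so that the intensity delivered can be reported as a range. If the present rule is kept, state there, and where the Background, study questions and Intervention section cite the percentage, that it is a percentage of the first failed weight.

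The cost is one sentence and two recorded weights per test, with no extra test, visit or participant. The downside is that the new rule can understate the maximum by up to one step, lowering the load by 0.75s kg at 75% and 0.5s kg at 50% in affected tests. It should be adopted for a correct label and a load based on demonstrated capacity, since it is no more precise than the present rule.

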### Procedures

Initially, the elderly women will answer a questionnaire for inclusion in the study and to characterize the study sample. Next, the elderly women were characterized as frail, pre-frail or non-frail according to the criteria proposed by Fried et al. (2001). Only those women classified as pre-frail will be invited to participate in the training program. All participants will undergo the TUG test [25,30,33], the 10MWT [34] and the knee extensor muscle strength test. Participants will also be tested with the isokinetic dynamometer at angular speeds of 60 and 180°/s and the plasma levels of IL-6 and TNF-α measured. All women will wear their everyday shoes or those that they consider the most comfortable.

For conducting the TUG test, the volunteer will be instructed to sit in a standard chair 45 cm in height with arm supports at a height of 65 cm (using the floor as a reference). At the verbal command "Are you ready? Go" the participant will stand, walk three meters (previously marked on the floor), turn, return to the chair and sit down again. A walking chronometer (*Q & Q, Japan CBM Corp*) will begin timing the moment the volunteer's trunk no longer touches the back of the chair, and will stop when the volunteer's trunk returns to leaning against the back of the chair. The displacement time in seconds will be noted for analysis.

Next, the 10MWT will be conducted. The volunteer will walk a course of ten meters (marked on a level floor), with two meters for acceleration and two meters for deceleration. The verbal command to begin will be the same as that used for the TUG test. The chronometer will begin as the volunteer passes the first two acceleration meters and will stop when the ten meters of the course are completed. The displacement time in seconds will be used for analysis. The volunteer will be instructed to walk at her normal pace.

To evaluate the knee extensor muscle strength, the volunteer will be positioned in the Biodex System 3 Pro^*® *^dynamometer chair. Her trunk will remain supported at 80° of hip flexion and will be secured with equipment positioning belts. She will be instructed to exert a maximum force and will be encouraged with handclaps and phrases such as "Let's go! Great. Don't stop." For each speed there will be a practice drill with three repetitions for familiarization. The test will be conducted by measuring five repetitions at an angular speed of 60°/s and fifteen repetitions an angular speeds of 180°/s, all at maximal effort, according to the assessment protocol that has previously been described [36]. The variables analyzed were the percentage of work normalized to body weight, the peak torque in Newton per meter (N/m) and the potential in watts (W).

The analysis of the plasma concentrations of IL-6 and TNF-α will be conducted in a laboratory on a different day than the functional and muscle strength measurements. These exams will be conducted in the morning, between 8:00 and 10:00 a.m., to guarantee that the circadian rhythm does not influence the measurements [37,38]. The volunteer will be instructed to eat normally the day before. A qualified professional will collect the blood, following the necessary patterns and procedures. Five milliliters of the collected blood will be centrifuged for 15 minutes and the plasma will be stored in a properly identified freezer (-70°C). Subsequently, duplicate analyses will be conducted using an ELISA with high sensitivity kits (Quantikine^®^HS, R&D Systems Minneapolis, USA) in accordance with the manufacturer's instructions and the analysis protocol. The results will be presented as the mean ± standard deviation.

### Sample size

The sample size was calculated after a previous pilot study with 12 participants, considering a confidence interval of 95%, a bilateral hypothesis test, a significance level of 0.05 (type I error), a power of 80% (type II error) and a crossover design for a statistical analysis of ANOVA. First, we calculated the size effect (f) for the partial ANOVA for the 12 participants, according to Portner & Watkins [39]. We use the functional performance (time in seconds of the TUG). We considered two freedom degrees and a power of 80%. It was determined that, considering a moderate effect size (0.5) for a minimum clinically significant difference, 13 volunteers will be needed in each group.

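### The sample-size statement calls 0.5 a moderate effect on the f scale and uses 2 df, so its 80% power is not shown for the randomised 13 v 13 comparison at ten weeks

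*Protocol article*

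**What the plan says.** The Sample size section of the protocol article gives these inputs:

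- a two-sided test ("a bilateral hypothesis test") and "a significance level of 0.05 (type I error)", with 80% power;
- the design and test: "a crossover design for a statistical analysis of ANOVA";
- the effect-size index: "we calculated the size effect (f) for the partial ANOVA for the 12 participants" of the pilot study, on Timed Up and Go (TUG) time;
- the degrees of freedom: "We considered two freedom degrees and a power of 80%";
- the result: "considering a moderate effect size (0.5) for a minimum clinically significant difference, 13 volunteers will be needed in each group".

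The sentence with the result does not repeat the index, but f is the only one the section names.

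The Sample section fixes the allocation: "These volunteers will be randomly divided into two groups (control = C and experimental = E) of 13 volunteers each". The Methods/Design section measures outcomes at ten weeks to capture the immediate effect of the exercise programme, and then switches the groups. The Statistical analysis section plans an ANOVA over three occasions: before the intervention, after it, and three months after its end.

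**The concern.** Three statements do not fit together.

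1. **Index and label.** For ANOVA, 0.25 is conventionally a medium f and 0.40 a large one, so f = 0.5 is large. A moderate 0.5 is the convention for d. With two equal groups f = d/2, so f = 0.5 means d = 1.0 and d = 0.5 means f = 0.25. The two readings differ by a factor of two in effect and about four in sample size.
2. **Degrees of freedom.** A comparison of two groups at one time has 1 df. Two df belong to three independent groups, to three occasions within women, or to a group-by-time interaction (2 − 1)(3 − 1). The section does not say which.
3. **Contrast.** The ten-week comparison sets training against no training between randomised groups before anyone switches. The section does not show that its 80% refers to that comparison.

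The 0.5 is presented as the smallest clinically significant difference. A null result could therefore be read as excluding a moderate effect when the ten-week comparison had little chance of finding one.

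**Working it through.** **Inputs.** Two-sided α = 0.05, target power 80%, effect size 0.5, 2 df and 13 per group (Sample size); two groups, 26 women (Sample); three occasions (Statistical analysis). The article gives no within-person correlation ρ, so every ρ below is an assumption.

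**Step 1: the plan's own figure.** For a one-way ANOVA with k independent groups of n, λ = f²kn with k − 1 and k(n − 1) df. Power is the probability that the noncentral F exceeds the central 95% point. With f = 0.5 and 2 df, k = 3:

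- n = 13: λ = 0.25 × 39 = 9.75, df 2 and 36, power 76.9%;
- n = 14: λ = 0.25 × 42 = 10.5, df 2 and 39, power 80.3%.

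The stated 13 is reproduced to within one woman per group, but for three groups (3 × 14 = 42 women). The trial has two.

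**Step 2: the ten-week comparison, unadjusted.** With k = 2 there is 1 df:

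- 0.5 is f (d = 1.0), n = 13: λ = 0.25 × 26 = 6.5, df 1 and 24, power 68.7%. At n = 16 power is 78.1% and at n = 17 it is 80.7%, so 17 per group are needed.
- 0.5 is d (f = 0.25), n = 13: λ = 0.0625 × 26 = 1.625, power 23.2%. For 80%, 64 per group are needed.

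**Step 3: 2 df as occasions or as group-by-time.** For three occasions in N women, λ = 3Nf²/(1 − ρ), with 2 and 2(N − g) df for g groups.

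| ρ (assumed) | f = 0.5, time effect in one group: women for 80% | f = 0.5, group-by-time: per group for 80% | f = 0.25, group-by-time: power with 26 women |
|---|---|---|---|
| 0 | 15 | 8 | 47% |
| 0.3 | 11 | 6 | 62% |
| 0.5 | 9 | 5 | 78% |
| 0.7 | 6 | 3 | 95% |

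At f = 0.5 the interaction needs at most 8 per group, and 26 women give at least 97.6%. A one-group time effect could return 13 at some ρ between 0 and 0.3, but as a single-group total with no comparison between arms. So f = 0.5 on these readings does not yield a requirement of 13 in each of two groups. With f = 0.25 the interaction does need 13 per group at ρ = 0.55 (82% power), but the section states 0.5.

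**Step 4: what 13 per group can detect at ten weeks.** For the two-sample t test the noncentrality is d√(13/2) with 24 df. With baseline ANCOVA it is d√(13/2)/√(1 − ρ²) with 23 df.

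| Analysis | Difference with 80% power | Power for 0.5 SD | Power for 1.0 SD |
|---|---|---|---|
| Unadjusted | 1.15 SD | 23% | 69% |
| ANCOVA, ρ = 0.5 (assumed) | 0.99 SD | 29% | 80.5% |
| ANCOVA, ρ = 0.7 (assumed) | 0.82 SD | 40% | 93% |

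**The case against.** The strongest reply is that the authors never planned a 1-df test at a single time. They name a crossover design and ANOVA, and three occasions match 2 df. On a group-by-time reading, 26 women have at least 97.6% power at f = 0.5. If a medium f = 0.25 was meant, a moderate effect, 2 df, two groups and 13 per group all agree at ρ = 0.55. A within-woman crossover comparison of all 26 (dz = d/√(2(1 − ρ)), 24 df) has at least 93% power for d = 1.0, and for d = 0.5 it has 41%, 69% and 88% at ρ = 0, 0.5 and 0.7. Baseline ANCOVA also reaches 80% for 1.0 SD at ρ = 0.5.

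Much of this stands. A reader might infer from the 69% and 23% that the planning figure is wrong or that 26 women are too few. The document does not support that, because those figures belong to one unadjusted comparison and the named design can do better.

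It does not repair the statement. The f = 0.25 reading changes the stated 0.5 and needs a correlation that appears nowhere. The crossover reading treats the experimental group's second period as an untreated control period, whereas Methods/Design reads it as longer-term outcome after training. A label that is right for d and wrong for f remains on any reading.

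The TUG standard deviation, the pilot values and a dropout allowance are also absent, but a condensed article may leave these to the full protocol. They are not part of this point.

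**Conclusion.** The point holds as an inconsistency in the stated justification. The effect size is named as f and labelled as if it were d. The 2 df do not match the two-group comparison at ten weeks. The stated inputs give 13 to 14 per group as a three-group calculation. The 80% power for a moderate effect is therefore not shown for the randomised 13 v 13 comparison, which has 69% power if 0.5 is f and 23% if it is d (unadjusted, two-sided 0.05, all 26 women analysed).

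These figures need no assumed correlation. Whether another contrast reaches 80% does: for group-by-time at f = 0.25, power runs from 47% at ρ = 0 to 95% at ρ = 0.7. The document settles neither the correlation nor the contrast, so it does not show that the trial is underpowered.

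**What to change.** Keep 26 women and rewrite the Sample size paragraph so that it:

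- says whether 0.5 is f or d, and labels it accordingly (large if f, moderate if d);
- names the contrast that the 80% covers (group-by-time, within-woman, or between groups at ten weeks), with its df and the assumed within-person correlation;
- adds a statement for the ten-week comparison, for example: *With 13 women per group, the comparison at ten weeks has 80% power for a difference of about 1.15 SD unadjusted, or about 0.8 to 1.0 SD with baseline ANCOVA if the correlation with baseline is 0.7 to 0.5. Power for a difference of 0.5 SD is 23% unadjusted and 29% to 40% with ANCOVA.*

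The cost is one paragraph and a less favourable stated power. No participants, visits or measurements are added.
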